## Introduction

Dementia is considered as a major public health concern.^1^ Due to the ageing population, the number of dementia cases will increase substantially in the next decades. In 2015, more than 46 million people worldwide were affected by dementia and this number is expected to increase to 131 million by 2050.^2^ This rise in people with dementia carries a high economic and social burden for society.^1^ In 2015, global costs of dementia reached 818 billion US dollars and will increase further.^3^ Currently, no curative treatments are available. Therefore, prevention is a key element to counteract the dementia epidemic.^4 5^

The most common types of dementia are Alzheimer’s disease (AD) (60%–70%), vascular dementia (VD) (15%–20%) or a combination of AD and VD (mixed dementia).^6–8^ The presence of a first-degree relative with AD doubles the risk for developing AD.^9^ This increased risk has several reasons. First, descendants of people with AD more often have a higher genetic predisposition for AD (eg, carrier of the apolipoprotein E (APOE) ε4 allele).^9^ Second, high blood pressure, vascular diseases and other vascular risk factors (ie, diabetes type 2, obesity, hypercholesterolemia) often cluster in families.^10^ Lastly, psychosocial behaviour runs in the family and also affects health behaviour and lifestyle.^11 12^ Not surprisingly, individuals with a parent who is recently diagnosed with AD or VD often worry about their own risk of developing dementia. Therefore, this life event (parental diagnosis of dementia) might encourage the willingness of individuals to change their health behaviour.^13^

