The first challenge of health behaviour change interventions is to achieve a high level of uptake for screening (eg, assessing risk and protective factors for dementia), reflecting the willingness to participate. A systematic review identified a large variation in uptake in health checks and lifestyle intervention programmes,^37^ depending on the type of recruitment strategy. The two main types of strategies for recruitment are the active and passive recruitment strategy. Active recruitment involves a personal invitation by the project staff and healthcare providers (eg, proactive) and passive recruitment involves recruitment of participants through various channels such as flyers and advertisements (eg, reactive).^38^ The most effective recruitment strategy is a proactive referral from a healthcare provider, while displaying posters and flyers showed to be less effective.^39 40^ Uptake also depends on other factors as described in social cognition models (eg, knowledge, perceived susceptibility and severity, facilitators, benefits and barriers and attitude towards such interventions).^32–36^ These factors are essential and useful to make a well-informed decision about dementia risk assessment, considering the possible benefits and harms. Therefore, information on dementia, the risk and protective factors for dementia, heritability and how to tackle risk and protective factors for dementia are important factors in the development of a web-based intervention. A previous study showed that the majority of the Dutch general population is unaware of the relationship between modifiable risk factors and brain health, particularly regarding major cardiovascular risk factors (eg, hypertension, hypercholesterolemia and coronary heart disease).^41^ It is shown that this lack of knowledge is a barrier to the uptake and maintenance of healthy behaviours for middle-aged individuals.^42^ Having a parent who is recently diagnosed with AD or VD could have led to an increased knowledge on dementia and risk perception.^13^ Therefore, middle-aged descendants of recently diagnosed people with AD or VD might be receptive to assess their risk and motivated to adopt a healthier lifestyle as they just realised their (familial) risk.^13 43^ Although we expect that the uptake in the active recruitment strategy will be higher compared with the passive recruitment strategy, participants recruited via the passive recruitment strategy might be more intrinsically motivated to adopt and maintain their healthy lifestyle and less likely to drop out of the study.

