
To our knowledge, none of the health behaviour intervention studies were aimed at a specific group of middle-aged adults with increased risk for dementia due to their parental family history of dementia. Therefore, this study aims to investigate the uptake and effectiveness of a tailor-made online lifestyle programme for dementia risk reduction (DRR) among middle-aged descendants of recently diagnosed (in the last 6 months) people with AD or VD in the Netherlands. This will give insight into what extent it is feasible to recruit middle-aged descendants of people with AD or VD at the memory clinics and whether these potential participants are willing to participate in a tailor-made online lifestyle programme in order to reduce their dementia risk.

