### Study population

Eligible participants are middle-aged individuals (40–60 years old) with a parent who is recently (less than 6 months ago) diagnosed with AD or VD (or mixed dementia) at one of the participating memory clinics in the Netherlands (see Acknowledgements section). Individuals should provide informed consent, be able to fill out an online Dutch questionnaire. Pregnant women are excluded from participation.

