### Statistical analyses

First, descriptive characteristics will be explored. The difference in uptake between the two recruitment strategies will be examined using multilevel logistic regression analyses in order to correct for clustering at memory clinic level. We will calculate the percentage with the corresponding 95% CI and use an alpha of 0.05 to test statistical significance.

The effectiveness of the online tailor-made lifestyle programme for DRR will be determined by, first comparing the change in LIBRA score, the individual risk factors and the MCLHB-DRR score between the active and passive recruitment strategy, and second comparing participants of the Demin study (active and passive recruitment strategy) to a control group consisting of Lifelines participants (large population-based cohort study (n>167 000)) (www.lifelines.nl)^64^ in outcome. Lifelines participants (age 40–60 years) with a parent with dementia will be matched (using propensity scores) on non-modifiable risk factors (age, gender and education) for dementia to participants of the Demin. Subsequently, multilevel analyses will be performed to examine the change in the LIBRA score and the individual health behaviours over time. In addition, possible confounding and interaction effects will be identified and corrected for in the analysis (eg, health literacy). We will calculate relative risks with 95% CIs and use an alpha of 0.05 to test significance.

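### The Lifelines controls carry no condition on how recently the parent was diagnosed, so the only comparison with people outside the programme cannot separate its effect from change after a recent parental diagnosis.

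*Protocol article*

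**What the plan says.** **Who enters Demin.** Under Study population in the Protocol article, participants are aged 40–60 "with a parent who is recently (less than 6 months ago) diagnosed with AD or VD" or mixed dementia. The aim at the end of the Introduction repeats the window: "middle-aged descendants of recently diagnosed (in the last 6 months) people with AD or VD in the Netherlands".

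**Why that window was chosen.** The Introduction says that "this life event (parental diagnosis of dementia) might encourage the willingness of individuals to change their health behaviour". It adds that middle-aged descendants of recently diagnosed people "might be receptive to assess their risk and motivated to adopt a healthier lifestyle as they just realised their (familial) risk".

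**Who the controls are.** Under Statistical analyses, "Lifelines participants (age 40–60 years) with a parent with dementia will be matched" to Demin participants by propensity score. The matching variables are age, gender and education. A general sentence then promises that confounding and interaction will be identified and corrected for, with health literacy as its example.

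**What the comparison is for.** The Abstract names the comparison with the matched Lifelines group as the way effectiveness will be evaluated. Statistical analyses lists two steps: active against passive recruitment, then all Demin participants against Lifelines. Study setting and design states that, once consent is signed, people from both recruitment strategies follow the same intervention.

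**The concern.** Recent parental diagnosis defines the Demin population, and the protocol links it to readiness to change behaviour. Change in behaviour and in the LIBRA score is what the effectiveness analysis measures. The characteristic is therefore fixed in one group, left open in the other, and plausibly related to the outcome.

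Analysing change from baseline does not remove the problem. It removes differences in starting level. It does not remove differences in expected course, and two people with the same baseline LIBRA score may follow different courses if one has just learned of a parent's dementia and the other has known for years.

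At stake is the effectiveness half of the stated aim. A difference from Lifelines could be read as the work of the programme when part of it would have followed the diagnosis anyway. A real benefit could also be hidden if the months after a diagnosis worsen some LIBRA components.

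**Working it through.** **Step 1: the two groups side by side.**

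| Feature | Demin | Lifelines controls |
|---|---|---|
| Age | 40–60 | 40–60 |
| Parent with dementia | required | required |
| Diagnosis within 6 months | required | no condition stated |
| Matched on | – | age, gender, education |
| Receives the programme | yes, both arms | serves as the control group |

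**Step 2: what each contrast estimates.** Take a simple additive description of mean change over follow-up: background change b, programme effect t, change d due to a recent parental diagnosis, and change v due to being someone who volunteers for a lifestyle programme. Let p be the share of Lifelines controls whose parent was recently diagnosed.

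- Demin: b + t + d + v
- Lifelines: b + p·d
- Difference: t + (1 − p)·d + v

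The recency bias is (1 − p)·d. It vanishes if p = 1 and equals d if p = 0. The documents give neither p nor d.

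For active against passive recruitment, t and d appear in both arms and cancel, leaving only the difference in v. That contrast cannot supply the missing estimate of t.

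**Step 3: direction.** The sign of d is open. Greater motivation would lower the LIBRA score. Low mood after a diagnosis would raise it through the depression item, which carries the largest risk weight in Table 3 (+2.1). Baseline also comes after the diagnosis, so part of either reaction may already be in the baseline value.

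**Step 4: scale, as illustration only.** The protocol states no sample size for the Lifelines comparison. Its total of 378 comes from the uptake calculation and reproduces: m = (15² + 25²)/(15 + 25) = 21.25; inflation 1 + (21.25 − 1) × 0.05 = 2.0125; 188 × 2.0125 = 378.35.

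Assume 378 Demin participants, 378 controls, no programme effect, no clustering and no dropout. Let s be the net bias favouring the programme, in SD of the change score. The chance of a two-sided 5% significant result in that direction is about Φ(s × √(378/2) − 1.96), with √189 = 13.75.

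| s (SD, assumed) | s × 13.75 | Chance of a significant result |
|---|---|---|
| 0.05 | 0.69 | 10% |
| 0.1 | 1.37 | 28% |
| 0.2 | 2.75 | 79% |
| 0.3 | 4.12 | 98% |

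None of these shifts comes from the documents. The table shows only that, at this sample size, a modest uncontrolled shift would matter. A shift in the other direction would work against the programme by the same amount.

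**The case against.** The strongest reply has four parts.

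- **The protocol's wording is cautious.** It says the diagnosis might encourage willingness to change. That can be read as a reason to offer a programme to this group, not as a forecast that behaviour changes without one. The article also names lack of knowledge as a barrier to healthy behaviour and calls behaviour change difficult. This stands. A reader might infer that the protocol treats the diagnosis as a trigger whose effect will be credited to the programme, but the text does not go that far. It supports only that the two cannot be told apart.
- **Nothing is known about the controls' timing.** A reader might infer that most controls are long past their parent's diagnosis. The article gives no such information, and recently affected controls are not excluded. This also stands: p is unknown, not small. But they are neither required nor identified, so the comparison does not control for recency.
- **Confounding will be corrected for.** The sentence is general, and health literacy is only an example. It does not repair this gap. Every Demin participant is inside the 6-month window, so adjustment needs controls known to be inside it too, and the article does not say that Lifelines records this.
- **The comparison is secondary and openly non-randomised.** True, and this limits the consequence. It does not change what the contrast can estimate.

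A reader might also fault the article for not aligning Lifelines follow-up with 12 months. A condensed article commonly leaves that detail to the full protocol or analysis plan, so it is not part of this point.

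**Conclusion.** The concern holds as a defect in a stated selection and matching rule. Followed as written, the Lifelines comparison estimates the programme effect together with (1 − p)·d and a volunteering component, and nothing in the article separates them. No size or direction can be given, because both p and d are absent from the documents.

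The conclusion rests on two things: that a recent parental diagnosis can affect later change, which the protocol's own rationale makes plausible but does not establish, and that not every control has a recently diagnosed parent, which follows from the absence of any such requirement. It does not show that an observed benefit would be spurious. Randomisation, the uptake outcome and the 378 target are untouched.

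**What to change.** **Preferred.** In Statistical analyses, restrict the Lifelines pool, where its data allow, to participants aged 40–60 whose parent's dementia is newly reported at the assessment used as their control baseline. This only approximates the 6-month window, since first report is not the date of diagnosis, and the text should say so. It also needs repeated family-history data, which the article does not describe, so availability must be checked first.

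Do this by restriction, not by adding recency to the propensity model. Time since diagnosis is under 6 months for every Demin participant, so the term is largely redundant once controls are restricted and lacks overlap if they are not.

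**If recency cannot be identified.** State that the contrast estimates the combined effect of the programme, a recent parental diagnosis and volunteering, and do not report it as programme effectiveness. This needs no new data.

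**Cost.** The first option shrinks the control pool by an unknown amount. The figure of more than 167 000 is the whole cohort, not the eligible part. The second option gives a narrower claim.

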**Methods and analysis:**

Demin is a cluster randomised controlled trial, aiming to include 21 memory clinics of which 13 will be randomly allocated to the passive (poster and flyer in a waiting room) and 8 to the active recruitment strategy (additional personal invitation by members of the team of the memory clinic). We aim to recruit 378 participants (40–60 years) with a parent who is recently diagnosed with Alzheimer’s disease or vascular dementia at one of the participating memory clinics. All participants receive a dementia risk assessment (online questionnaire, physical examination and blood sample) and subsequently an online tailor-made lifestyle advice regarding protective (Mediterranean diet, low/moderate alcohol consumption and high cognitive activity) and risk factors (physical inactivity, smoking, loneliness, cardiovascular diseases (CVD), hypertension, high cholesterol, diabetes, obesity, renal dysfunction and depression) for dementia. The primary outcome is the difference in uptake between the two recruitment strategies. Secondary outcomes are change(s) in (1) the Lifestyle for Brain Health score, (2) individual health behaviours, (3) health beliefs and attitudes towards DRR and (4) compliance to the tailor-made lifestyle advice. Outcomes will be measured at 3, 6, 9 and 12 months after baseline. The effectiveness of this online tailor-made lifestyle programme will be evaluated by comparing Demin participants to a matched control group (lifelines cohort).

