Patients with AD or VD (or their caregivers) receive an envelope either at the registration desk of the memory clinic or after the consult of the patient (only with active recruitment). This envelope is addressed to the middle-aged descendants of patients with recently diagnosed AD or VD and includes a patient information form (PIF) with information about the content of the study, the advantages and disadvantages of study participation and how potential participants can participate. Potential participants (one family member per patient) are asked to register themselves (eg, making an account) on the Demin website (www.demin.nl), by using the memory clinic specific login access code, which is reported on the front page of the PIF and represents the memory clinic in which the parent was diagnosed. The decision to participate is confirmed by the participants by signing the online informed consent form (electronic signature by using SMS-tan). After signing this form, individuals from both recruitment strategies are able to log in to their personalised website ‘My Demin’ and continue the intervention in an equal manner. The personalised website ‘My Demin’ is secured and only accessible for the participant by logging in with their personal email address, password and SMS-tan code. ‘My Demin’ contains the following information: (1) My personal (account) information, (2) Message inbox, (3) My online questionnaires, and (4) My personal health profile including online tailor-made lifestyle advice. After participants have completed the online questionnaire, they automatically receive a message with a request to make an appointment for physical examination including a fasting blood sample. Moreover, participants can invite siblings to participate in the study in ‘My Demin’.

The functionalities provided by the Demin website are based on the literature and input we received from people with a parent with dementia (focus group discussions).

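### The only comparison with no programme is non-randomised and matched on age, gender and education alone, with no stated handling of baseline LIBRA or lifestyle

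*Protocol article*

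**What the plan says.** The Statistical analyses section of the protocol article describes two effectiveness comparisons. The first is active against passive recruitment. The second is "comparing participants of the Demin study (active and passive recruitment strategy) to a control group consisting of Lifelines participants". The control pool is "Lifelines participants (age 40–60 years) with a parent with dementia", and these people "will be matched (using propensity scores) on non-modifiable risk factors (age, gender and education". No modifiable factor is listed for matching.

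The outcome analysis follows: "multilevel analyses will be performed to examine the change in the LIBRA score and the individual health behaviours over time". Beyond matching, the one safeguard is that "possible confounding and interaction effects will be identified and corrected for in the analysis (eg, health literacy". The only effect measure named is in the closing sentence: "We will calculate relative risks with 95% CIs and use an alpha of 0.05 to test significance".

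Two other places show that neither randomised arm goes without the programme. The abstract states: "All participants receive a dementia risk assessment (online questionnaire, physical examination and blood sample) and subsequently an online tailor-made lifestyle advice". Study setting and design says that, after consent, "individuals from both recruitment strategies are able to log in to their personalised website", and that both groups then continue in the same way.

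**The concern.** Active against passive recruitment compares two routes into the same programme. It cannot show that the programme works better than none. That question rests on the Lifelines contrast, which is observational, so its credibility depends on the covariates used for matching and adjustment.

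The stated matching set omits the baseline value of the outcome and every component of it. A person's room to change depends on where they start. LIBRA is a sum of threshold items, so someone who does not smoke and has a BMI below 30 cannot improve on those two items.

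The protocol also gives reasons to expect the groups to differ. Study population requires a parental diagnosis less than 6 months old, whereas Lifelines controls need only have a parent with dementia. The Introduction expects recent diagnosis to make descendants receptive and motivated. The sample size section assumes uptake of 30% and 50%, so half or more of those eligible are expected not to join. What is at stake is whether a difference in LIBRA change can be read as an effect of the programme or only as a difference between volunteers and cohort members.

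**Working it through.** **Plan's own figure.** The protocol gives none for the Lifelines comparison. Its sample size concerns uptake only (188 × 2.0125 = 378.35, stated as 378) and does not bear on this point.

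**What the matching leaves out.** Table 3 scores 12 items, all under the heading of modifiable factors. The risk items sum to 1.0 + 1.1 + 1.1 + 1.3 + 1.4 + 1.5 + 1.6 + 1.6 + 2.1 = 12.7 and the protective items to −3.2 − 1.7 − 1.0 = −5.9, which is the stated range. None of the 12 is a matching variable.

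**Inputs for the illustration.** The documents give no LIBRA standard deviation, baseline gap or correlation over time, so these are assumptions:
- d, the baseline gap (Demin minus Lifelines): ±0.5 or ±1 point.
- r, the correlation between baseline and follow-up: 0.5 to 0.9, with equal variances at both times.
- No true programme effect.

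**Case A: the gap arises by selection on the observed score.** The expected follow-up gap is r × d.
- Difference in change: r × d − d = −(1 − r) × d.
- Baseline-adjusted difference: r × d − r × d = 0.

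| Size of d | r = 0.5 | 0.6 | 0.7 | 0.8 | 0.9 |
|---|---|---|---|---|---|
| 0.5 | 0.25 | 0.20 | 0.15 | 0.10 | 0.05 |
| 1 | 0.50 | 0.40 | 0.30 | 0.20 | 0.10 |

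The entries are the size of the spurious difference in change, and its sign is opposite to d. A higher LIBRA score means higher risk. Healthier volunteers (d below zero) would therefore make the programme look worse than it is, and less healthy volunteers would make it look better.

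A simulation of this case, with an assumed SD of 2.5 and a gap of about ±0.5, gave change-score biases of 0.197 and −0.196 at r = 0.6, and 0.102 and −0.097 at r = 0.8. Adjusting for baseline left between −0.001 and 0.002.

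**Case B: the two populations differ by a stable amount d.** The follow-up gap is also d.
- Difference in change: d − d = 0.
- Baseline-adjusted difference: d − r × d = (1 − r) × d.

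Here the change score is unbiased, and baseline adjustment produces an error of the same size as in the table, with the same sign as d. The simulation did not cover this case. The two estimators thus err in opposite directions under the two assumptions, and the documents do not say which applies.

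**Scale.** The smallest Table 3 weight is 1.0. A mean shift of 0.05 points equals 1 in 20 participants changing status on such an item (0.05/1.0), and 0.5 points equals 1 in 2 (0.5/1.0).

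**Effect measure.** Relative risks suit the dichotomous items in Table 3, such as current smoking or BMI of 30 or more. They do not suit LIBRA change, weekly minutes of activity or the 0–14 diet score listed under Secondary outcomes.

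**The case against.** The best defence is that the plan does more than match. It restricts controls by age and parental dementia and promises to correct for confounding. Model covariates are often left to an analysis plan, and none is shown here. This stands in part: a reader might infer that confounding is ignored, and the text does not support that. But the matching rule is stated outright and confined to non-modifiable factors, and the general promise names neither baseline LIBRA nor lifestyle.

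A reader might also infer that regression to the mean is built in. It is not. Study population sets no LIBRA or lifestyle entry threshold, so the effect arises only if the groups differ at baseline through selection on the observed score. Under a stable difference, baseline adjustment is what misleads (Case B). This objection stands, and it is why baseline adjustment alone is not a sufficient remedy. Nor would adjustment remove motivation that acts on change independently of the starting score.

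A third tempting step is to convert the illustrative bias into dementia risk using the protocol's 19% per point. The trial does not estimate dementia risk, and the gap is assumed, so that conversion adds nothing.

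Finally, it would be too strong to call relative risks wrong for the whole analysis. They are valid for the binary risk factors. What remains is that no other measure is named for outcomes that are mostly continuous.

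**Conclusion.** The point holds in limited form. The sole contrast with no programme is non-randomised, its stated matching set leaves out the baseline value and all components of the outcome, and no stated adjustment fills the gap. The bias is of unknown size and direction. The range of 0.05–0.5 LIBRA points is an illustration that rests on an assumed gap of 0.5–1 point, selection on the observed score, and a correlation of 0.5–0.9. The documents do not establish that a gap of that size exists. Confounding by motivation would remain even after baseline adjustment. The primary outcome, uptake, is untouched; what is weakened is the claim of effectiveness.

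**What to change.** - Add baseline LIBRA, and those of its components available in both sources, to the propensity score, the outcome model or both. Some baseline LIBRA value must be obtainable in Lifelines, since change is to be compared. The protocol does not say which components Lifelines holds, how they were measured or at what interval, so this should be stated.
- Fix the covariate set before Demin follow-up data are seen, and report covariate balance after matching.
- Present the baseline-adjusted estimate and the change-score (difference-in-differences) estimate together, each with its assumption. Agreement would strengthen the conclusion, and disagreement would show how far it depends on the assumption.
- Label the comparison non-randomised, with residual confounding by motivation after a recent parental diagnosis.
- Report mean differences with confidence intervals for continuous outcomes, and keep relative risks for binary ones.

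The cost is more analysis work and somewhat fewer close matches. The figure of more than 167 000 is the whole cohort. The usable pool is those aged 40–60 with a parent with dementia, and its size is not stated, so the loss cannot be quantified. Handling baseline in the outcome model rather than in the matching avoids that loss.

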### Randomisation of memory clinics

To prevent contamination between the two recruitment strategies, randomisation is performed at the level of the memory clinics. To enhance comparability between the intervention (participants of the active recruitment strategy) and control group (participants of the passive recruitment strategy), the memory clinics will be matched and randomised by a statistician, who is blind to the identity of the memory clinics and not involved in the study. First, all participating memory clinics will be matched into pairs based on the following criteria: (1) number of newly diagnosed dementia (VD, AD or mixed dementia) patients seen per year (range vary from 60 to 350 patients per year) and (2) the average social economic position (SEP) of the population living around the memory clinic (neighbourhood SEP), based on data from Statistics Netherlands.^44^ Second, the matched memory clinics will be randomised (pairwise randomisation) to an active recruitment strategy or passive recruitment strategy using a computer-generated random number list. As we expect a higher response rate in the active recruitment strategy group, we use an active:passive recruitment strategy ratio of 8:13 (see sample size calculations).

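### Clinics are matched on volume and neighbourhood SEP before randomisation, but the primary uptake model as described adjusts only for clinic clustering, so its test is conservative and its interval too wide if those factors predict uptake

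*Protocol article*

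**What the plan says.** Under Randomisation of memory clinics, the article says that "all participating memory clinics will be matched into pairs based on the following criteria": first the "number of newly diagnosed dementia (VD, AD or mixed dementia) patients seen per year", with a stated range of 60 to 350, and second "the average social economic position (SEP) of the population living around the memory clinic (neighbourhood SEP". Then "the matched memory clinics will be randomised (pairwise randomisation" to active or passive recruitment, and "we use an active:passive recruitment strategy ratio of 8:13".

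Under Statistical analyses, the first paragraph gives the primary analysis of uptake as "multilevel logistic regression analyses in order to correct for clustering at memory clinic level", tested at 0.05. It names no covariate and no pair or stratum term.

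The second paragraph of that section covers programme effectiveness: change in LIBRA score, individual risk factors and MCLHB-DRR score between the two strategies, then Demin participants against propensity-matched Lifelines participants. Here the article adds that "possible confounding and interaction effects will be identified and corrected for in the analysis (eg, health literacy". Health literacy is the only example given.

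**The concern.** Matching makes the two arms more alike on volume and SEP. If those factors predict uptake, the true sampling variance of the arm difference falls. A model that ignores them leaves their contribution in the between-clinic variance, so it estimates the standard error as if the clinics had not been matched. The estimate stays unbiased, but the test rejects too rarely and the interval is wider than the design warrants. With 21 clinics, clinic-level variance dominates the uptake comparison, so this is where precision can be recovered. Both factors must be known for every clinic before allocation, so using them needs no new data.

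The second matter is separate and confined to the effectiveness paragraph. Once an arm-by-covariate term enters a model, the arm coefficient becomes the effect at one value of that covariate. That changes the quantity reported as the main result; it does not remove a distortion.

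**Working it through.** **The plan's own figure.** From Sample size calculations: m = (15² + 25²)/(15 + 25) = 21.25. Inflation factor = 1 + (21.25 − 1) × 0.05 = 2.0125. Total = 188 × 2.0125 = 378.35, stated as 378. The calculation reproduces and takes no credit for matching, so this point does not disturb it.

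**How much variance lies between clinics.** Uptake is measured against all eligible people, and the article gives no mean number eligible per clinic. Two assumed values bracket it:
- 50, implied by the sample size section: 15/0.30 = 50 and 25/0.50 = 50.
- 205, the midpoint of the stated volume range: (60 + 350)/2 = 205.

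Between-clinic share of the variance of a clinic's uptake = ICC/(ICC + (1 − ICC)/n):
- n = 50: 0.05/(0.05 + 0.95/50) = 72%.
- n = 205: 0.05/(0.05 + 0.95/205) = 92%.

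**Does the proposed model use up too much?** Degrees of freedom fall from 21 − 2 = 19 to 21 − 4 = 17, and the critical t rises from 2.09 to 2.11.

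**Simulation of the matched design.** There were 21 clinics, ordered on the sum of two standardised factors and cut into eight adjacent sets of two or three, with one clinic per set drawn as active (8:13). This layout is an assumption. Clinic uptake was analysed as a proportion, as a stand-in for the multilevel logistic model, with total variance 0.24, ICC 0.05, equal clinic sizes and 8,000 runs per scenario. R² is the assumed share of between-clinic variance that the two factors explain; the article gives no value. Each cell shows unadjusted / adjusted.

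| Eligible per clinic | R² | Type I error | 95% CI half-width, points | Power, 10-point difference | Power, 20-point difference |
|---|---|---|---|---|---|
| 50 | 0 | 4.9% / 4.7% | 11.9 / 12.4 | 37% / 35% | 91% / 88% |
| 50 | 0.2 | 3.4% / 4.9% | 12.0 / 11.5 | 37% / 40% | 91% / 92% |
| 50 | 0.4 | 2.2% / 5.0% | 12.0 / 10.5 | 35% / 47% | 93% / 96% |
| 205 | 0 | 4.3% / 4.6% | 10.6 / 11.0 | 45% / 43% | 96% / 94% |
| 205 | 0.2 | 3.2% / 4.8% | 10.7 / 10.0 | 44% / 50% | 97% / 97% |
| 205 | 0.4 | 1.9% / 5.3% | 10.7 / 8.8 | 44% / 61% | 98% / 99% |

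Adjusting shortens the half-width by (12.03 − 11.52)/12.03 = 4% at the low end (50 eligible, R² = 0.2) and by (10.72 − 8.79)/10.72 = 18% at the high end (205 eligible, R² = 0.4).

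**Where the gain comes from.** The actual spread of the estimate hardly moves: at 205 eligible and R² = 0.4 its standard deviation is 4.28 points with or without adjustment. Matching has already delivered the balance. Adjusting makes the reported standard error agree with it.

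**A less favourable setting.** A second simulation used the 15 and 25 included participants as clinic sizes, with eight pairs plus five extra passive clinics. Type I error was 4.1% / 5.2% at R² = 0.25 and 3.0% / 5.2% at R² = 0.50. Power at 20 points was 77% / 78% and 79% / 85%. At R² = 0 adjusting cost 4 points (76% / 72%). Those counts are not the denominator of uptake, so the table above is closer to the primary outcome.

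**The case against.** The strongest reply is that only a journal article is shown, and a covariate list is ordinarily left to the SAP. The phrase about clustering explains why the model is multilevel; it does not say that clustering is the only thing modelled. That is fair. A reader might infer that volume and SEP have been deliberately excluded, and the text does not support that: they are unnamed, not ruled out. What stands is that the article fixes the matching factors in the design and describes the primary model without them. Analysing by what was matched on follows from the design, unlike the choice of other prognostic covariates.

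Four stronger readings are tempting and should not be drawn.
- **That the confounder and interaction search affects the primary result.** It appears only in the effectiveness paragraph.
- **That terms will be selected by significance.** The article says only that they will be identified, which could mean from the literature.
- **That false interactions are likely to a known degree.** With k independent tests at 0.05 the chance of at least one is 1 − 0.95^k: 5% for one, 23% for five, 40% for ten. The article gives no count and one example, so no single figure can be attributed to it. Nor would omitting the matching factors create false interactions.
- **That adjusting removes 18 to 37% of the variance** (0.915 × 0.2 and 0.915 × 0.4). That describes estimated variance, at an assumed 205 eligible per clinic; the true variance has already been reduced by matching.

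Looking for confounders is itself proper here. The Lifelines comparison is not randomised, and participants in the two strategies select themselves after clinics are allocated.

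**Conclusion.** The point holds in a limited form. As described, the primary analysis is valid but conservative if clinic volume and neighbourhood SEP predict uptake. At an assumed R² of 0.2 to 0.4, type I error is about 2 to 4% and adjustment shortens the interval by about 4 to 18%. At the planned 20-point difference, power is about 90% or more for 50 to 205 eligible per clinic and moves by only a few points. The benefit is mainly a narrower interval and better power for smaller differences. All of this rests on the unknown R², the assumed numbers eligible, the ICC of 0.05 and an assumed matching layout. If the factors explain nothing, adjustment is slightly harmful.

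No bias or inflated false-positive rate follows for uptake. The interaction wording is a lesser point, about what the main effectiveness estimate will mean. The change is worth making because it is cheap; the trial does not depend on it.

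**What to change.** State the primary model as arm, clinic volume and neighbourhood SEP as fixed effects, with a random clinic effect, and use the same two covariates in the other active-versus-passive comparisons. Adjusting for the factors is more workable than pair effects: eight one-to-one pairs use 16 clinics, which leaves 21 − 16 = 5 passive clinics without a partner.

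In the effectiveness paragraph, separate the two ideas. Name in advance the confounders for the Lifelines comparison. List any interactions of interest, including health literacy, as exploratory, and keep them out of the model that gives the main estimate.

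The cost is a few lines of text and two of 19 cluster-level degrees of freedom. If the factors turn out not to predict uptake, about 0.4 to 0.5 points of half-width and about 1 to 3 points of power are lost (4 in the less favourable setting). No design change or new data collection is needed.
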